## Abstract

**Background:**

Poor governance and accountability compromise young democracies’ efforts to provide public services critical for human development, including water, sanitation, health, and education. Evidence shows that accountability agencies like superior audit institutions can reduce corruption and waste in federal grant programs financing service infrastructure. However, little is know about their effect on compliance with grant reporting and resource allocation requirements, or about the causal mechanisms. This study protocol for an exploratory randomized controlled trial tests the hypothesis that federal and state audits increase compliance with a federal grant program to improve municipal service infrastructure serving marginalized households.

**Methods/Design:**

The AUDIT study is a block randomized, controlled, three-arm parallel group exploratory trial. A convenience sample of 5 municipalities in each of 17 states in Mexico (*n*=85) were block randomized to be audited by federal auditors (*n*=17), by state auditors (*n*=17), and a control condition outside the annual program of audits (*n*=51) in a 1:1:3 ratio. Replicable and verifiable randomization was performed using publicly available lottery numbers. Audited municipalities were included in the national program of audits and received standard audits on their use of federal public service infrastructure grants. Municipalities receiving moderate levels of grant transfers were recruited, as these were outside the auditing sampling frame – and hence audit program – or had negligible probabilities of ever being audited. The primary outcome measures capture compliance with the grant program and markers for the causal mechanisms, including deterrence and information effects. Secondary outcome measure include differences in audit reports across federal and state auditors, and measures like career concerns, political promotions, and political clientelism capturing synergistic effects with municipal accountability systems. The survey firm and research assistants assessing outcomes were blind to treatment status.

**Discussion:**

This study will improve our understanding of local accountability systems for public service delivery in the 17 states under study, and may have downstream policy implications. The study design also demonstrates the use of verifiable and replicable randomization, and of sequentially partitioned hypotheses to reduce the Type I error rate in multiple hypothesis tests.

**Trial registration:**

Controlled-trials.com Identifier ISRCTN22381841: Date registered 02/11/2012

**Electronic supplementary material:**

The online version of this article (doi:10.1186/1471-2458-14-912) contains supplementary material, which is available to authorized users.

## Background

Many young democracies seem to be doing a poor job of delivering social services critical to human development, including water, sanitation, health, and education [1, 2]. One explanation is poor governance and accountability in public service provision [3–8]. In principle democracy causes rulers to act in the best interest of the majority, via periodic contested elections [9, 10]. In practice elections are blunt instruments of accountability [10–12]. Young democracies, in particular, often suffer from unstable party systems, lack of programmatic political platforms, deep inequality, ethnic tensions, and pervasive clientelism that compromise accountability [13, 14]. The task is further complicated by the magnitude of the challenge young democracies face, and the very nature of public service provision which includes long agency chains, multiple stake holders, hard to measure and verify multifaceted outcomes, and many tiers of management far removed from front line workers [1, 3]. Researchers have proposed accountability agencies as a useful institutional remedy capable of helping young democracies consolidate electoral accountability and improve service delivery [15, 16]. These are independent, non-elective, specialized bodies of oversight that provide relevant information on government performance, and sometimes sanction public officials on voter’s behalf [17–19]. Examples include election commissions, superior audit institutions (SAIs), anticorruption bodies, courts, human rights commissions, and statistical offices. Given young democracies’ weak electoral accountability, the magnitude of the tasks they face, and the complex nature of public service provision there is a manifest need for solid evidence on the effect of accountability agencies on public service delivery [10].

Evidence suggests SAIs are effective in reducing corruption and waste in public service infrastructure investment and in procurement of inputs. SAIs are external public auditors that monitor public expenditures and performance, often on behalf of the Legislature. For example, an increase in “audit intensity” put in place by the city of Buenos Aires reduced prices paid by local hospitals for basic, homogeneous inputs by 10–15 percent in the short term [20]. Experimental evidence has also shown how a 100 percent probability of an audit reduced missing expenditures in an Indonesian road construction project by some eight percentage points [21]. Another experiment in Brazil finds that “increasing audit risk by about 20 percentage points reduced the proportion of non-competitive procurement modalities adopted by local managers by about 17 percent [and] reduced the proportion of local procurement processes involving waste or corruption by about 20 percent” [22]. However, the experiment found no effect on the quality of publicly provided preventive and primary health care services, measured using client satisfaction surveys, nor on local compliance with national guidelines for the conditional cash transfer program Bolsa Família, measured in terms of beneficiary recruitment and enforcement of conditionalities. Additional evidence suggests the effectiveness of SAIs may be moderated by organizational features [23–26], and the degree of electoral competition in the polity [27]. These determine the objectivity, independence, and autonomy of the SAI. Experimental evidence also identifies synergistic effects between audits and municipal accountability systems [28–31].

There remain important gaps in this body of evidence. First, the mechanisms by which SAIs improve service delivery remains unclear. The economic approach to crime suggests wages, audit probabilities, and the degree of punishment deter dissonant behaviour by public employees and elected officials [32, 33]. But this ignores other causal channels, like knowledge acquisition by audited entities and changed perceptions about their administrative capacity. It also makes strong assumptions about the information and cognitive abilities available to agents. And it assumes negative audit reports will result in credible punishment, which is not always credible in young democracies. Second, most studies focus on the effect of SAIs on waste and corruption, yet SAIs can also ensure that services reach their intended beneficiaries by monitoring administrative compliance with national guidelines. Typically these stipulate what services are to be provided, how, and to whom. Third, the extant experimental evidence relates to marginal increases in the probability of audit and not the overall effect of the national program of audits (versus no program of audits). Besides, some experimental manipulations are unrealistic, like increasing audit probabilities to 100 percent. Fourth, some evidence points to synergistic effects between audits and municipal accountability systems [34] but whether these generalize to contexts where elected officials are limited to non-consecutive terms is an open question.

This study protocol for a block randomized, controlled, exploratory trial randomly assigns study municipalities in Mexico to be audited by federal auditors, by state auditors, and a control outside the national program of audits. It addresses three objectives: to identify the reduced-form impacts of randomized assignment to audits on outcomes such as knowledge about program requirements, compliance with the law and capacity building; as well as municipal governments’ spending priorities, and actual spending patterns. Second, to identify the reduced-form impacts of assignment to audit by either the federal or a state level SAI on audit verdicts, including the number of observations made, their severity, and the amounts of mandated reimbursements to federal treasury of misspent grant money. Third, to test for the effect of audits on career prospects, and on state governors’ discretionary allocations to municipalities. Table 1 provides list a pre-specified set of expected outcome hypotheses designed to meet these objectives.

**Table 1 Tab1:** **AUDIT study hypotheses**

	Primary objective: Impact evaluation
H1	Municipal administrators in treated municipalities are aware of
	their treatment status
H2	Municipal administrators in treated municipalities audited in year 1
	believe the probability of being audited in year 2 is lower than in
	year 3
H3	Municipal administrators in treated municipalities have higher
	long-run beliefs about the probability of being audited
H4	Municipal administrators in treated municipalities have higher
	knowledge of FISM grant rules and regulations
H5	Municipal administrators in treated municipalities manifest
	preferences for municipal investments more in accordance with
	FISM priorities
H6	Municipal administrators in treated municipalities are more
	aware of lack of capacity and more likely to manifest plans for
	improving capacity
H7	Municipal administrators in treated municipalities are more likely
	to comply with FISM reporting and data accessibility rules
H8	Audited municipalities report allocating more FISM investment
	funds to localities outside the council seat and to public goods

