### Outcome measures

The primary outcome measures of this study capture the effectiveness of the national program of audits amongst the study group. Primary outcomes follow an expected causal order, going from how audits may affect subjects’ beliefs about future audits, to how they modify subjects’ knowledge of program rules, investment preferences, awareness of capacity limitations, compliance with reporting requirements, and the actual allocation of investments between outlying settlements and the council seat (see Table 1). Secondary outcomes compare the effectiveness with which the federal and state level auditors uncover wrongdoings; the severity with which they judge them; and the diligence with which they pursue wrongdoings. (If solid evidence of differences is found, we will do some additional exploratory work, like subgroup analysis by stratifying on the basis of an institutional quality index [44]). Tertiary outcomes explore possible interactions between audits and local accountability systems. We do so by comparing how audits may affect subject’s expectations about future political appointments, career prospects, perceive their principals differently, and whether state governors engage in clientelist practices to blunt the effect of audits on municipalities of their same political persuasion. Due to their specificity most outcome measures were defined and measured by the investigators using a proprietary survey, and related measurement instruments. Specific definitions, measurements, and sources are described in Additional file 2.

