Our outcome data come from routine audit reports, other official sources, direct observations by the investigators, and from a proprietary survey of municipal administrators. The survey was developed by the investigators and implemented by the Mexican survey firm *Data Opinion Publica y Mercados*. The survey firm was blind to treatment status. The survey was pilot tested on four municipalities similar to the ones in the experimental group, and the results where used to clarify the meaning of questions and adapt the length of the survey, as well the contact strategy. The survey was fielded over the phone between April 27, 2012 and June 7, 2012. We administered the survey to key personnel in each municipality, including: the Municipal President, Treasurer, Director of Public Services, Director of Public Works, and/or Director of Urban Planning. It was not always possible to contact the personnel, in which case we moved down the municipal hierarchy. Given the sample size of this study, strenuous efforts were made to ensure full response. A copy of the survey is included in Additional file 3. Data from official sources will be collected by a research assistant according to guidelines provided by the researchers. Some data will be collected through direct observations (e.g. does municipality have a web page) according to a measurement instrument developed by the researchers and implemented by a research assistant. Collection of these data is expected to end on January 30, 2013. The research assistant is blind to treatment status. Finally, most outcomes of interest are subjective in nature. This introduces some well known limitations.

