### Interference

Interference occurs when outcomes for any given unit depend, not only on its own treatment status, but also on the profile of treatments for others units in the experimental group. In the extreme case where control units benefit as much as the treated units from a given treatment profile the estimated ATE will be zero even though the treatment might have been hugely beneficial. There is an effect but no primary effect (conditional on interference) [57]. To test for the presence of interference and control for it we need to assume a model of interference. In our discussion with employees of the ASF we learned that municipal officials talk to each other with regards to the audit program. We will assume talking is along party lines and limited to other municipalities in the same state (parties are organized around states). (Geographic distance between municipalities may not be that important considering the degree of cell phone and email penetration in Mexico but we might consider it in a secondary analysis). We will also assume that the intensity of talking depends on the similarity of the municipalities, as they are more likely to have interests in common. We will proxy for similarity using FISM grant amounts. These are decided by a formula (and some gubernatorial discretion) that takes as inputs socio-economic indicators. We check for interference using municipalities outside the experimental group (their exposure is random [52]) using administrative data from the Federal Treasury detailing what categories of municipal public goods municipalities invest in and their rate of disbursements. Specifically we proceed as follows: We define the distance measure for municipality *i* in experimental state *j* as , where *x*_*i**j*_=1 if at least one of the audited municipalities in state *j* has a major with the same party affiliation as municipality *i*, and where  is the amount of FISM transfers (*w*_*i**j*_) received by municipality *i* in state *j* as a fraction of the average transfer received by audited municipalities of the same party affiliation () in the same state *j*. If none of the audited municipalities share a party affiliation we set *y*_*i**j*_=0. To ensure *y*_*i**j*_∈ [ 1,0) we only calculate the measure for municipalities that receive same or lower transfers than those in the experimental group.Since our distance measure is continuous, we stratify municipalities into quartiles defined by *y*. Along with the binary *x*, this defines a 4×2 table of outcomes, where one column is units treated with spillover effects of magnitude *y*_*q*_ and the other column is assumed to receive no spillover.As noted, dependent variables will be derived from the PASH files which cover almost all municipalities in Mexico. These include whether municipalities report to the Federal Treasury, what categories of municipal public goods they invest in, and the rate of disbursements among other.

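### H8 tests reported allocations but is described as actual allocation; and if H8 exists only for municipalities that report, the planned bounds depend on a weak test

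*Protocol article*

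**What the plan says.** Table 1 of the Protocol article lists H8 under the primary objective: "Audited municipalities report allocating more FISM investment" funds to localities outside the council seat and to public goods. Two other places describe the same outcome differently. The objectives in the Background promise effects on "spending priorities, and actual spending patterns". The Outcome measures section ends its list of primary outcomes with "the actual allocation of investments between outlying settlements and the council seat".

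That section also says "Primary outcomes follow an expected causal order", and places compliance with reporting requirements directly before allocation. The compliance step is H7: administrators in treated municipalities are more likely "to comply with FISM reporting and data accessibility rules".

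On sources, the article says "Our outcome data come from routine audit reports, other official sources, direct observations by the investigators, and from a proprietary survey of municipal administrators". It does not match these to individual hypotheses; definitions and sources are left to Additional file 2.

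The Attrition section tests the sharp null that treatment does not affect attrition and takes non-rejection as strong support for comparable arms. The item containing extreme bounds opens with the condition that this null is rejected.

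**The concern.** There are two separate issues.

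**Measurement.** A reported allocation and an actual allocation are different quantities. The reporting party is the one being audited, on the use of these same funds. H4 and H7 are routes by which an audited municipality could describe, classify or document the same projects differently without moving any money. A positive H8 would then be read as money reaching outlying settlements when only the paperwork changed. H8 is the only primary hypothesis about where the money goes, so this wording decides what the trial can claim on its main policy question.

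**Selection, if it applies.** Should H8 data exist only for municipalities that report, the set observed in each arm is itself determined after randomisation, and H7 predicts that it differs by arm. A comparison among reporters would then not be protected by randomisation. The protocol does not connect H7 with the availability of H8.

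**Working it through.** The article gives no figure on this point and states that no power analysis was done. The first step therefore compares texts, and the second is an illustration on assumed reporting rates.

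**1. Reported or actual.** Table 1 says municipalities report the allocation. The objectives and Outcome measures call it actual. The Discussion opens by naming measurement error as a threat, but its subsections deal with attrition, non-compliance and interference. Audit reports, one of the listed sources, could not serve as an even-handed check, because the control arm is by design outside the audit programme. Bounds for missing data do not help either: they cover values not observed, not values observed but reported differently.

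**2. How often would the attrition rule trigger, and how much is at stake?**

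Inputs from the article: 17 federal + 17 state = 34 audited, and 51 controls (34 + 51 = 85). Assumed: reporting rates p_c (control) and p_t (audited), and a correlation ρ between the propensity to report and the share allocated outside the seat. The audit is given no true effect on allocation.

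- Power of a two-sided 5% comparison of reporting rates: Φ[(p_t − p_c − 1.96·SE₀)/SE₁], with SE₀ pooled and SE₁ unpooled. For 60% v 80% the pooled rate is (51×0.60 + 34×0.80)/85 = 0.68, SE₀ = √(0.68×0.32×(1/51 + 1/34)) = 0.103 and SE₁ = √(0.24/51 + 0.16/34) = 0.097. Power is 0.49. This approximates the planned randomisation test and ignores blocking.
- Width of extreme bounds for a share between 0 and 1: (1 − p_c) + (1 − p_t).
- Spurious reporters-only difference in SD units, if a municipality reports when a standard normal propensity exceeds a threshold: ρ × [φ(z_t)/p_t − φ(z_c)/p_c], where φ(z)/p is the mean propensity among the reporting fraction p. For 60% v 80% and ρ = 0.5: 0.5 × (0.350 − 0.644) = −0.15.

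| Reporting, control v audited (assumed) | Power of attrition test | Width of extreme bounds | Spurious difference, ρ = 0.3 | ρ = 0.5 |
|---|---|---|---|---|
| 60% v 80% | 0.49 | 0.60 | −0.09 SD | −0.15 SD |
| 70% v 85% | 0.35 | 0.45 | −0.07 | −0.11 |
| 75% v 90% | 0.40 | 0.35 | −0.07 | −0.11 |
| 80% v 95% | 0.50 | 0.25 | −0.07 | −0.12 |
| 90% v 97% | 0.21 | 0.13 | −0.04 | −0.06 |
| 95% v 99% | 0.14 | 0.06 | −0.02 | −0.04 |

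In every row reporting truly differs by arm, yet the test misses this at least half the time. The sign is negative because ρ is taken as positive; it would reverse with ρ.

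**3. A tempting repair, checked.** One could count unreported money as zero so that all 85 municipalities have a value. Assume reporting of 50% v 70%, with municipalities that report in either arm placing 40% outside the seat, those that report only if audited placing 30%, and no true effect. Controls score 0.5×40 = 20. Audited municipalities score 0.5×40 + 0.2×30 = 26. The result is a spurious +6 points in the hypothesised direction. Among reporters the difference is 26/0.7 − 40 = −2.9 points. The repair replaces one bias with a larger one.

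**The case against.** A reader might infer that H8 does compare self-selected reporters and so cannot say anything about spending. The article does not support that. Nothing restricts H8 to reporters; its source is left to Additional file 2, and if it comes from the survey, reporting to the Treasury does not decide whether it is observed. The Treasury (PASH) files are said to cover almost all municipalities, though that remark belongs to the interference check on municipalities outside the experimental group. H7 also covers data accessibility and need not be a yes/no reporting indicator. All of this stands, and it makes the selection issue conditional. It does not remove it: the same text lists reporting as a variable, "These include whether municipalities report to the Federal Treasury", so being covered by the files is not the same as reporting.

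Next, the Attrition section already provides for treatment-related missing outcomes, including extreme and trimmed bounds. This is largely right. What remains is the trigger: bounds follow a rejection, the test is weak at this sample size, and H7 already predicts that its null is false.

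Last, *actual* may be meant only as a contrast with the stated preferences of H5. That is a fair reading of the authors' intent, and Table 1 is open about reporting. Even so, the published conclusion would be read literally, and neither place where the word appears limits it to what is reported.

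**Conclusion.** The measurement point holds on the article's own wording and needs no assumption: H8 can support a conclusion about reported allocations, and nothing described extends that to actual ones. How far documentation alone could move H8 cannot be sized from the article.

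The selection point holds only if H8 is missing for non-reporters. Its size is then unknown. On the assumed rates the spurious difference runs from about 0.02 SD with near-universal reporting to about 0.15 SD at 60% v 80%, and extreme bounds from 0.06 to 0.60 wide. For scale, a simple comparison of 34 with 51 municipalities detects (1.96 + 0.84)×√(1/34 + 1/51) = 0.62 SD with 80% power, so this bias alone would not usually produce a significant result. The firmer fault is the rule: bounds that wait for a test with about 14% to 50% power will often not be shown when they are needed. With high reporting the bounds could be informative, so it would be wrong to say that selection makes H8 uninterpretable.

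**What to change.** 1. In the objectives and in Outcome measures, replace *actual* with *reported* for this outcome, and limit the H8 conclusion to reported allocations.
2. For any H8 analysis restricted to municipalities that report, state that non-reporters count as missing and always show the Attrition section's bounds beside the estimate, whatever the attrition test shows. Give reporting rates by arm with it.
3. Do not make a variable that scores unreported money as zero the primary H8 outcome. It merges H7 into H8 and can be positive through reporting alone.

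The trial is at the analysis stage, so this takes two changes of wording and one standing display from methods already planned. The price is a narrower stated conclusion and, if reporting is low, bounds too wide to settle the question.
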